## Abstract

**Background:**

People with dementia are often inapproachable due to symptoms of their illness. Therefore nurses should establish relationships with dementia patients via their remaining resources and facilitate communication. In order to achieve this, different targeted non-pharmacological interventions are recommended and practiced. However there is no sufficient evidence about the efficacy of most of these interventions. A number of publications highlight the urgent need for methodological sound studies so that more robust conclusions may be drawn.

**Methods/Design:**

The trial is designed as a cluster randomized controlled trial with 20 nursing homes in Saxony and Saxony-Anhalt (Germany) as the units of randomization. Nursing homes will be randomly allocated into 4 study groups consisting of 5 clusters and 90 residents: snoezelen, structured reminiscence therapy, 10-minutes activation or unstructured verbal communication (control group). The purpose is to determine whether the interventions are effective to reduce apathy in long-term care residents with dementia (N = 360) as the main outcome measure. Assessments will be done at baseline, 3, 6 and 12 months after beginning of the interventions.

**Discussion:**

This trial will particularly contribute to the evidence on efficacy of non-pharmacological interventions in dementia care.

**Trial Registration:**

ClinicalTrials.gov NCT00653731

## Background

Dementia is one of the most frequent and serious diseases occurring in people of higher age. There are currently more than 6 million people with dementia in the European Union with the prevalence of the disease increasing in the next decades [1].

People with dementia are often inapproachable due to symptoms of their illness. Besides cognitive disorders, primarily the non-cognitive symptoms of dementia, such as apathy, anxiety, depression, and challenging behavior, complicate the course of the disease and impede communication. Therefore nurses should establish relationships with dementia patients via their remaining resources and facilitate communication. Emotions, memories, important characteristics of the patients' biography, as well as perceptions on the somatic and emotional level can be used as resources in order to approach persons with dementia by using different pathways, even if communicative relationships are seemingly impeded.

In order to achieve this, different conceptualized non-pharmacological interventions are recommended in practice guidelines and practiced [2,3]. However, there is no sufficient evidence about the efficacy of several of these interventions, such as snoezelen and reminiscence therapy [4-7]. A number of publications highlight the urgent need for methodological sound studies so that more robust conclusions may be drawn [8,9].

The purpose of this study is to determine whether the interventions of snoezelen/multisensory stimulation, structured reminiscence therapy, and 10-minutes activation [10] are effective to reduce apathy in long term care residents with dementia.

## Methods

### Study design

A cluster randomized controlled trial with nursing homes as clusters is designed to verify the effects of 3 individual interventions: structured reminiscence therapy, 10-minutes activation and snoezelen. In order to preclude that the effects arise only due to the intensified social contacts, analogous individual contacts are implemented in the control group via unstructured verbal communication.

It is hypothesized that the interventions will have a positive impact on apathy in long term care residents with dementia in comparison to the control group. The primary outcome measures apathy after 12 months.

### Inclusion of clusters

A cluster is defined either as a nursing home by itself or a working ward of a large nursing home. None of the clusters may share facilities or staff.

10 nursing homes in the areas of Leipzig, Saxony, and Halle, Saxony-Anhalt (Germany) respectively, will be recruited that have implemented none of the study interventions in routine care prior to the study.

### Recruitment of individual participants

The identification and complete inclusion of participants must be done before cluster randomization to avoid foreknowledge of allocation and to reduce selection bias and empty randomized clusters [11,12].

Information and instruction of the participants will be done personally and in written form by trained nursing home staff, the consent to participate [13] will be obtained in writing from the residents. In case guardians are appointed, they will be informed about the possibility of taking part in the trial and will be asked for a participation of their charge in the trial.

In the total 20 nursing homes all residents fulfilling the inclusion criteria (suffering from dementia, informed consent in person or by legal guardian, age: ≥ 55 years) will be assessed using the *Mini Mental State Examination - MMSE *[14] or the *MMSE version for vision impairment - MMblind *[15] by the external investigators. Exclusion criteria are Korsakoff's syndrome or cognitive impairments from other causes than dementia.

Then from each cluster 18 participating residents with a cut-off value MMSE ≤ 24 or MMblind ≤ 17 [15] will be included using computer-generated random number tables.

### Cluster randomization

The 20 included nursing homes will be randomized into 4 study groups consisting of 5 clusters each, stratified according to province:

▪ structured reminiscence therapy (experimental group 1),

▪ 10-minutes activation (experimental group 2),

▪ snoezelen (experimental group 3),

▪ unstructured verbal communication (control group).

An individual randomization on the resident level does not seem possible out of methodical and practical reasons. A clear distinction between individual interventions on the resident level cannot be assumed in the training of different nurses in different interventions within one institution. Therefore, to avoid contamination and to achieve a feasible approach a cluster randomization design is chosen.

For concealed allocation of clusters the randomization list will be computer-generated by the Institute of Medical Epidemiology, Biostatistics, and Informatics, Halle/Saale, which is blind to the identity of the nursing homes and the included residents, after all baseline measurements.

The summary of the study design is presented in Figure 1.

**Figure 1 F1:**
[figure not shown]
**Study design**.

### Study procedure

In each of the 20 included nursing home clusters 6 registered nurses will be selected and trained in the intervention their cluster will be randomized to. Nurses in the experimental groups receive training by external experts. Training takes place in three-day courses outside the facility. Instead of three-day training, nurses in the control group clusters will receive a one-day instruction on performing conversation-based individual contacts relating to everyday life.

After the training, the interventions in each of the participating nursing homes will be monitored by the investigators in order to evaluate the training effects. This is to secure that the interventions are carried out consistently and on the same level.

The interventions in the experimental groups will be carried out once or twice a week as one-to-one sessions by the trained nursing staff, over a period of 20 or 10 minutes over 12 months. This period was selected according to the intervention type and regards the feasibility in the nursing homes considering the time and personal resources.

In order to examine the possibility that effects can be observed solely due to intensified social contacts, the control group is designed as sham intervention on the basis of 20-minutes individual contacts once a week offering topical conversations.

Nursing staff will have to fill in a continuous documentation form about the topics and characteristics of every intervention session for every participating resident, including the case and reason of possible non-conduction. This documentation is intended to support the resident related intervention strategy and to enable a detailed data analysis about realized interventions.

All intervention facts are summarized in Table 1.

**Table 1 T1:** Scheme of the study groups: study intervention program

Experimental group 1 (N = 5 nursing homes): Structured reminiscence therapy	
Education	3 days; 6 caregivers per nursing home
Intervention	• one-to-one session as an individual nursing intervention
	• once a week for 20 minutes
	• 3 residents per caregiver
Procedure	The aim of reminiscence is to stimulate memory and mood of demented people in the context of resident's life history, if applicable with the aid of sensory stimuli, e.g. photographs.
	
**Experimental group 2 (N = 5 nursing homes): 10-minutes activation**	
Education	3 days; 6 caregivers per nursing home
Intervention	• one-to-one session as an individual nursing intervention
	• twice a week for 10 minutes
	• 3 residents per caregiver
Procedure	The aim is to stimulate memory and all senses (visual, auditory, tactile and so on) by the use of different stimuli related to the resident and physical activation.
	

**Experimental group 3 (N = 5 nursing homes): Snoezelen**	
Education	3 days; 6 caregivers per nursing home
Intervention	• one-to-one session as an individual nursing intervention
	• once a week for 20 minutes
	• 3 residents per caregiver
Procedure	The aim is to improve the well-being of demented people by positive stimulation of their senses (visual, auditory, tactile, olfactory and gustatory stimulation) with different materials in a multisensory stimulation room or in the resident's room with a mobile snoezelen unit.
	

**Control Group (N = 5 nursing homes): Unstructured verbal communication**	
Instruction	1 day; 6 caregivers per nursing home
Active comparator	• one-to-one session as an individual nursing intervention
	• once a week for 20 minutes
	• 3 residents per caregiver
Procedure	The participants in the control group receive individual contacts with the same intensity by verbal conversation about everyday life without specific strategies.

### Measures

Evaluation of the interventions will be done on resident and staff level. Four points of measurement are scheduled in the trial: baseline assessment and measurements after 3, 6, and 12 months after intervention begin (see Figure 2).

**Figure 2 F2:**
[figure not shown]
**Points of measurement and outcome measures**.

The primary outcome measure is apathy after 12 months using the German version of the *Apathy Evaluation Scale - AES *[16,17]. Data collection will be done by interviews of the nursing staff.

Secondary outcome measures on the resident level are behavioral disturbances, isolated aggressive events and well-being.

Behavioral disturbances will be measured using the *Neuropsychiatric Inventory (Nursing Home) - NPI-NH *[18]. The instrument is a caregiver-based rating scale to evaluate 12 neuropsychiatric symptoms in patients with dementia: delusions, hallucinations, agitation, depression, anxiety, apathy, irritability, euphoria, disinhibition, aberrant motor behavior, night-time behavior disturbances, and appetite and eating abnormalities. Isolated aggressive events will be continuously documented by the staff members using the *Staff Observation Aggression Scale-Revised - SOAS-R *[19]. This instrument is to monitor the frequency, nature, and severity of aggressive incidents. Well-being will be measured using a Likert-type *Smiley Face Rating Scale *- *SRS *range from 1 to 4 marks by the residents.

Socio-demographic data like age, gender, and treatment data will be assessed and documented thoroughly in a Case Report Form, including the German versions of the *Clinical Dementia Rating *- *CDR *[20,21] and the *Care Dependency Scale: Pflegeabhängigkeitsskala *- *PAS *[22,23]. As a progressive course of disease can be assumed, a final assessment to the most important treatment data (i.e., MMSE, CDR, PAS) will be done for a better interpretation of results.

As further secondary outcome measures on staff level the health-related quality of life using the *Nottingham Health Profile *- *NHP *[24,25] as well as the evaluation of the subjective work pressure with subscales of the *Potentialanalyse stationärer Altenpflege - PASTA *[26] will be measured on the basis of a self-evaluation. It can be assumed that due to the increase of successful communication and the reduction of challenging behavior in residents with dementia, physical and mental strains of caregivers will be reduced and their health-related quality of life will increase or the strain caused by their job's tasks will be reduced.

### Sample size calculation

It is assumed that people with mild to moderate dementia have a mean apathy score *AES *of 45 [16]. To detect a mean reduction of the apathy score from 45 to 35 points (23%) with standard deviation (SD) 12 points between one intervention and one control group we need 13 residents in 10 nursing homes. The power of 80% for a cluster randomized t-test with a significance level alpha = 0.016 (0.05/3) is obtained with assumed intra-cluster correlation coefficient of ICCC = 0.05. The number of nursing homes increases to 20 (4 groups consisting of 5 nursing homes each) as there are three intervention groups and one control group and all intervention groups are tested against the same control group. Considering a mortality rate of 40%, the number of required study participants in each nursing home increases to 18 residents with dementia and thus to a total sample size of N = 360 residents (20 nursing homes * 18 residents).

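### Three comparisons with one shared control are planned at a flat Bonferroni level of 0.016: valid, but a step-down test would gain power at no cost

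*Protocol article*

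**What the plan says.** The Sample size calculation section of the protocol article sizes one intervention against control for a fall of 10 points in mean AES, 45 down to 35. It takes "standard deviation (SD) 12 points between one intervention and one control group" and an "assumed intra-cluster correlation coefficient of ICCC = 0.05". The stated power is 80%, using a "cluster randomized t-test with a significance level alpha = 0.016 (0.05/3"), and the result is that "we need 13 residents in 10 nursing homes". The design then grows to 20 homes, five per group, because "all intervention groups are tested against the same control group". An allowance for 40% mortality raises enrolment to 18 residents per home.

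The Data analysis section names mixed models and tests of time, intervention and their interaction. It gives no multiplicity procedure, so 0.016 is the only test level in the article. Whether tests are one- or two-sided is not stated.

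**The concern.** A flat split of 5% over three tests leaves part of the permitted error unused, for two reasons. First, the three contrasts share the same control homes, so with equal groups their estimates are correlated at 0.5, and Bonferroni takes no account of this. Second, once one arm has been shown effective, fewer hypotheses remain, yet a flat rule keeps the three-way level for the rest. A smaller matter is that 0.05/3 is 0.0167, so 0.016 is a truncation.

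With five homes per group and heavy expected mortality, power is scarce. The Study design section hypothesizes that the interventions as a group will help, so several effective arms is the plan's own expectation, and that is where a flat rule loses most.

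**Working it through.** **Inputs from the Sample size calculation section:** difference 10 points, SD 12, ICC 0.05, 5 homes per group, 13 evaluable residents per home, level 0.016. Enrolling 18 and losing 40% leaves 18 × 0.6 = 10.8 per home, so both 13 and 10.8 are shown.

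**Assumptions, not in the article:** two-sided tests, and between-home variance pooled over four groups, giving 4 × (5 − 1) = 16 degrees of freedom (df).

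**1. The plan's own 80%.** At 13 per home:
- Design effect = 1 + 12 × 0.05 = 1.6.
- Standard error = 12 × √(2 × 1.6/65) = 2.66.
- Noncentrality = 10/2.66 = 3.76.

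Two-sided power at 0.016 is 74.3% on the 8 df of a two-group test with 10 homes, 84.1% on 16 df, and 91.1% by normal approximation. One-sided on 8 df it is 85.3%. The formula that adds one cluster per group gives 4.745, rounded up to 5 homes, with power 82.9%. The stated 80% lies within this range, but no variant tried lands within 2 points of it. The comparison below does not depend on which was used.

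**2. Error actually spent.** The three levels sum to 3 × 0.016 = 0.048. With the shared control, simulated familywise error when no intervention works is 4.1% on 16 df, and 4.3% either by normal approximation or with separate 8-df tests.

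**3. Critical values on 16 df, two-sided.**

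| Rule | Largest statistic | Second | Third |
|---|---|---|---|
| Flat 0.016 | 2.693 | 2.693 | 2.693 |
| Holm (0.05/3, 0.05/2, 0.05) | 2.673 | 2.473 | 2.120 |
| Step-down Dunnett | 2.593 | 2.424 | 2.120 |

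The Dunnett values correspond to per-test levels of 0.0196, 0.0276 and 0.05. They lie below the flat value at every step, so on the same statistics nothing is lost. Simulated familywise error is 5.0% when no arm works and at most 4.8% when one or two do.

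**4. Power per effective arm** (400,000 simulated trials per scenario, 16 df).

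| Residents per home | Flat 0.016 | Step-down Dunnett: one arm works | Two work | Three work |
|---|---|---|---|---|
| 13 | 84.1% | 86.4% | 88.6% | 91.5% |
| 10.8 | 79.1% | 81.8% | 84.5% | 87.8% |

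At 13 per home the gains are 2.3, 4.5 and 7.3 points. Under the normal approximation they shrink to 1.1, 2.5 and 4.3.

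**5. Where the gain comes from.** Power to show all three effective arms at 10.8 per home, 16 df:
- flat 0.016: 62.1%
- flat 0.05/3: 62.8%
- single-step Dunnett (correlation, no stepping): 65.9%
- Holm (stepping, no correlation): 79.6%
- step-down Dunnett (both): 80.2%

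Stepping alone supplies 79.6 − 62.8 = 16.8 of the 18.1 points, and using the correlation on top of it adds 0.6. The order reverses when only one arm works: Holm stays near 80% at 10.8 per home while step-down Dunnett reaches about 82%. At 13 per home the one-arm figures are 84.6% and 86.4%. Truncation alone costs about half a point per comparison (0.2 to 0.7 across the variants).

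**The case against.** The strongest reply is that nothing here is wrong. Bonferroni is valid for any correlation, protects the familywise error and is conventional. That stands: a reader might infer that the plan mishandles multiplicity or inflates error, and the article supports neither.

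A second reply is that 0.016 appears only as a sample size input. Sizing at Bonferroni and analysing by Holm or Dunnett would fit the text, and an unseen analysis plan may say so. This also stands. That the strictest level will be kept for every arm after a first rejection is an inference from the only rule given, not something the article states.

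Third, the largest figures are easily over-read. The rise from 62% to 80% requires all three interventions to achieve the full 10 points and concerns showing all three, a target the plan does not set. It also cannot be credited to the ignored correlation, since Holm delivers almost all of it. The chance of finding at least one effective arm when all three work moves only from 93.2% to 94.6%.

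Fourth, the baselines of 84% and 79% rest on 16 df. The two-group test the plan describes has 8 df, giving about 74% at 13 per home and 69% at 10.8. Comparing step-down Dunnett with those figures would overstate its benefit, because about 10 points of the difference at 13 per home come from pooling variance over four groups.

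What survives is that, like for like, the step-down test is more powerful at the same 5% and needs no extra homes or residents.

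**Conclusion.** The point holds as lost efficiency. The gain per effective arm is 2 to 3 points if one intervention works and 7 to 9 if all three do, assuming two-sided tests, 16 home-level df, balanced groups and the plan's effect, SD and ICC. On the normal approximation it is about 1 to 4 points. The direction does not depend on the df chosen; the size does. At 10.8 residents per home and 16 df, the change moves power per comparison from just under the plan's 80% target to just over it. The truncation to 0.016 is a matter of notation more than substance. It is a worthwhile, nearly free improvement, and the plan's control of error is sound without it.

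**What to change.** Before outcome data are seen, state that the three primary intervention-versus-control contrasts are tested by a step-down procedure at 5% two-sided familywise error:
- Use step-down Dunnett on contrasts from the single four-arm mixed model, with home-level degrees of freedom (about 16, or 15 with a province term), not resident-level ones.
- Use Holm instead if the joint distribution is not to be relied on, for example because uneven deaths disturb the balance. It keeps most of the gain when several arms work and little when only one does.
- Report adjusted p-values. Label any simultaneous confidence intervals as single-step Dunnett, and warn that they may not match every step-down rejection.
- If Bonferroni remains the basis of the sample size statement, write 0.0167.

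The cost is a sentence or two in the analysis plan and standard software. The number of homes and residents is unchanged.

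### Enrolling 18 residents per home does not preserve the required 13 at 40% mortality: about 10.8 are expected to remain, and 18 covers at most 27.8% loss

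*Protocol article*

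**What the plan says.** All the figures are in the Sample size calculation section of the protocol article.

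- Base requirement for one pairwise comparison: "between one intervention and one control group we need 13 residents in 10 nursing homes". This is read as 13 in each of 10 homes, 5 per arm.
- Effect and spread: "To detect a mean reduction of the apathy score from 45 to 35 points (23%) with standard deviation (SD) 12 points".
- Error rates: "The power of 80% for a cluster randomized t-test with a significance level alpha = 0.016 (0.05/3"), with an intra-cluster correlation of 0.05. Neither sidedness nor degrees of freedom are given.
- Allowance for deaths: "Considering a mortality rate of 40%, the number of required study participants in each nursing home increases to 18 residents with dementia".
- Result: "a total sample size of N = 360 residents (20 nursing homes * 18 residents").

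The enrolled number recurs in Recruitment of individual participants ("Then from each cluster 18 participating residents with a cut-off value MMSE ≤ 24") and in the abstract ("4 study groups consisting of 5 clusters and 90 residents"). The primary outcome is the AES apathy score at 12 months.

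**The concern.** An allowance for loss has to be set so that the residents who remain meet the requirement. That means dividing the requirement by the retained fraction. Multiplying it by one plus the loss fraction gives a smaller number, and at 40% loss the gap is large. Here the section names 13 as the number needed and 40% as the loss, but the number it enrols does not return 13 once that loss is taken.

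This section is the only justification given for N = 360, and the Publication policy section commits to reporting the results in the context of this protocol. If 40% mortality occurs as assumed, the 12-month analysis will rest on fewer residents than the section says are required. The quoted power would then refer to a sample that the design does not expect to have.

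**Working it through.** **Inputs, all from the Sample size calculation section.** Required per home m = 13; 5 homes per arm; difference 45 − 35 = 10; SD 12; ICC 0.05; alpha 0.016; loss 40%; enrolled 18 per home.

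**1. Reproducing the printed 18**

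- 13 × (1 + 0.40) = 18.2, which rounds to 18. Over 20 homes this is 364, against the printed 360.
- 13 / (1 − 0.40) = 21.7, i.e. 22. Over 20 homes this is 440.

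The printed figure matches the first route and not the second. The formula is not printed, so the route is an inference. The next step does not depend on it.

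**2. What 18 delivers**

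- Expected remaining per home: 18 × 0.6 = 10.8
- Per arm: 5 × 10.8 = 54, against 5 × 13 = 65, which is 17% fewer
- Over 20 homes: 216, against 260
- Largest loss that still leaves 13: 1 − 13/18 = 27.8%

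**3. Effect on power**

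Formulas: design effect = 1 + (m − 1) × 0.05; SE = 12 × √(2 × design effect / (5m)); noncentrality = 10 / SE.

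| Evaluable per home | Design effect | SE | Noncentrality |
|---|---|---|---|
| 13 | 1.60 | 2.66 | 3.76 |
| 10.8 | 1.49 | 2.82 | 3.55 |

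The protocol does not state the test variant, so four are shown at alpha 0.016. The 8 df come from the 10 homes of one comparison (10 − 2), and the 16 df from pooling the variance over all 20 homes in four groups (20 − 4). The t-test rows use the noncentral t distribution.

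| Variant | Power at 13 | Power at 10.8 |
|---|---|---|
| Two-sided t, 8 df | 74% | 69% |
| Two-sided t, 16 df | 84% | 79% |
| Two-sided normal | 91% | 87% |
| One-sided t, 8 df | 85% | 81% |

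The loss from 13 to 10.8 is about 4 to 6 percentage points in each row.

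**4. Smallest difference detectable with 80% power (two-sided)**

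| Variant | At 13 | At 10.8 |
|---|---|---|
| t, 8 df | 10.6 points | 11.3 points |
| t, 16 df | 9.5 points | 10.1 points |

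**5. The base figure of 13**

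None of the variants tried gives exactly 13 as the minimum per home for 80% power. At alpha 0.016 the minimum is 9 for the two-sided normal approximation, 11 for the one-sided t on 8 df and 17 for the two-sided t on 8 df. The 13 is therefore taken as given, and the four variants cannot be narrowed to one from the text.

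**The case against.** **The power may still be adequate.** This stands. At 10.8 per home, power stays above 80% under the normal approximation and under the one-sided t-test on 8 df, and at 16 df it is 79%. A reader might infer from the 69% on 8 df that the mortality step brings the trial down from 80% to 69%. The documents do not support that. On 8 df the full 13 per home already gives only 74%, so about half of that gap is there before any resident is lost. It belongs to the choice of degrees of freedom, which is a separate matter.

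**Residents who die still contribute data.** This stands in part. The Drop-outs section keeps data up to the point of drop-out, assessments are planned at baseline, 3, 6 and 12 months, and the Data analysis section allows mixed models. Power based on 10.8 completers may therefore be pessimistic. The protocol gives no correlation between visits, so the recovery cannot be sized, and the sample size section claims no credit for it. It does not restore 13 observed scores at 12 months.

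**Eighteen was set by staffing.** Table 1 gives 6 caregivers × 3 residents = 18 per home, so this is plausible. The sample size section nevertheless derives 18 from mortality, and that derivation fails whatever the practical reason was.

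**The 40% may refer to another period.** No period is given. Because the figure is used only to inflate the sample for a 12-month endpoint, loss by 12 months is the natural reading. If another period is meant, the text should say so.

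**Conclusion.** The inconsistency is real and lies within one section. The requirement of 13 per home, 40% mortality and 18 enrolled cannot all hold. At the stated mortality about 10.8 per home (54 per arm) are expected instead of 13 (65 per arm), and 18 covers at most 27.8% loss. Losses for reasons other than death would come on top.

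The consequence for power is modest: about 4 to 6 percentage points under the plan's own difference, SD, ICC and alpha. It is not established that the trial falls below 80%, because that turns on sidedness and degrees of freedom, which the protocol does not state.

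The conclusion assumes that 13 means per home, that the 40% applies by 12 months, and that the power calculation counts only residents with a 12-month score. The multiplication by 1.4 is a likely explanation of the 18, not a premise.

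**What to change.** Keep N = 360 and correct the Sample size calculation section in one of two ways:

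- say that 18 per home preserves 13 evaluable residents at a loss of up to about 28%; or
- keep the 40% and say that about 10.8 per home (54 per arm) are expected to be evaluable at 12 months. Give the power and the smallest detectable difference under a declared test, with sidedness and degrees of freedom. On a two-sided t-test at alpha 0.016, the detectable difference is about 11.3 points on 8 df or 10.1 on 16 df, against 10.6 or 9.5 at 13 per home.

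In either case, state the period to which the mortality figure refers.

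The cost is wording and a slightly less favourable stated figure. No further residents are needed, and the design, endpoint and analysis do not change.

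Twenty-two per home (20 × 22 = 440) is only the arithmetic consequence of keeping both 13 and 40%, and is not recommended here. It leaves 22 × 0.6 = 13.2 per home, which gives about 75% power on a two-sided t-test with 8 df, so it would not by itself secure 80% on that variant. It also would not fit the 6 × 3 scheme in Table 1.
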